#### Secondary Outcomes

##### Onset of Mood Events

The incidence of mood events of participants in each group (MoodBox group, online psychoeducation group, and naturalistic observation group) during the follow-up period will be assessed by (a) depressive episode: meet the diagnosis of a depressive episode as measured by PHQ-9 diagnostic algorithm or according to the DSM-IV diagnostic criteria; (b) hypomania or manic episode: the Altman Self-Rating Mania Scale (ASRM) scale total score ≥ 5 or meet the diagnosis of hypomania or manic episode based on DSM-IV diagnostic criteria.

ASRM is a five-item mania self-rating scale for assessing the severity of mania or hypomania (26). A cutoff score of 5 or higher indicates a high probability of a manic or hypomanic condition (based on a sensitivity rating of 85.5% and a specificity rating of 87.3%).

##### Response Rate

The response rate is defined as the proportion of participants who do not meet the criteria of subclinical depression of each study group during the follow-up period. The efficacy of the continuous intervention is defined as the participants showed a decrease of depression symptoms measured by PHQ-9 (less than two items of the scale score ≥ 2 and the total score <5) for all the post-treatment follow-up assessments after completing 8 weeks' intervention.

##### Participant Adherence to the Intervention

The adherence of participants to the assigned intervention will be measured by the usage of the intervention website. Specifically, we will measure the frequency of log-in, duration of website use, and completeness of homework.

##### Participant Satisfaction and Acceptability for the Intervention

The satisfaction and acceptability of the intervention will be assessed by questionnaires at the end of the intervention. In the questionnaire, the researchers asked about “how easy is it for you to understand the content?,” “how easy is it for you to use the program?,” “do you feel the program can help you manage your mental difficulties?,” “do you want to use the program in the future?,” and “will you recommend the program to other people?.” The participants will be asked to answer each question in a scale of 1–5. Qualitative interviews will also be conducted with participants who are willing to participate.

##### Contributing Factors of Subclinical Depression

In order to identify the contributing factors of subclinical depression, psychosocial outcomes including anxiety, life events, attachment style, coping style, and parenting style will also be assessed, which will be measured by the Generalized Anxiety Scale (GAD)-7, the Life Event Scale (LES), Childhood Trauma Questionnaire (CTQ), the Inventory of Parent and Peer Attachment (IPPA), Egna Minnen Beträffande Uppfostran (“own memories of parental rearing practices in childhood,” EMBU), and Coping Style Questionnaire (CSQ), relatively. The Generalized Anxiety Disorder-7 (GAD-7) is a seven-item self-report scale for assessing the severity of anxiety. Each item is scored from 0 to 3, with a total score of 21 (27). The Chinese version of the scale established good reliability (Cronbach's α = 0.90) (28). Negative life events will be measured by LES, a 48-item self-report scale to measure positive and negative life events (29). The scale measures events regarding serious illness, housing, relationships and social difficulties, relationship breakdowns, unemployment, and financial crisis. Childhood traumatic experiences will be assessed by CTQ (30). The CTQ consists of 28 items, with each item scored from 1 to 5 with a total score of 125. Attachment will be measured using IPPA, a 25-item scale consisting of two core components: parent attachments and peer attachments (31). The EMBU is used to measure perceived parents' raring behaviors (32), with a questionnaire comprising 81 questions and 15 subscales covering raring behaviors such as overinvolvement, affection, overprotectiveness, guilt engendering, and rejection. Coping strategies will be assessed using CSQ (33). The CSQ consists of 20 items to assess different ways of coping, with each item having four response options: “never used,” “occasionally used,” “sometimes used,” and “often used.”

### Statistical Consideration

Data management and statistical analysis will be conducted using SAS9.4 (SAS Institute Inc., Cary, NC, USA). The sample characteristics would be compared using chi-square test for categorical variables or using Fisher's Z test when needed; ANOVA tests for normal distributed variables; and Mann–Whitney's U test for non-normal distributed variables. Analysis of efficacy will be based on an intent-to-treat principle, comprising all participants randomized regardless of the treatment group. The Kaplan–Meier survival analysis will be used to calculate the estimated time from baseline to response during 8 weeks' follow-up.

The Cox proportional hazard regression model using the Breslow method will be used to compare estimated time to response between groups, with control for covariates such as age, gender, years of education, and disease-related conditions; also we would use the exact method as sensitive analysis in case of tied survival data. Considering the long interval between visits after week 8, we will also use maximum likelihood estimation for Cox hazard regression model following Shen's work (34) to control left interval truncated data. Secondary analyses will be performed to assess changes from baseline to the endpoint of the study on scores of scales, using mixed-effects model for repeated-measures analysis (MMRM). A *p*-value <0.05 is considered as statistically significant. The Bonferroni method will be used to control multiple comparisons of type I error inflation.

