## Methods

### Study Design

The study is a multicenter, randomized, controlled, non-blinded superiority study with three parallel groups. People with subclinical depression will be invited to participate in the study. Eligible participants will be randomly assigned to one of the three groups—the MoodBox group, the online psychoeducation group, and the naturalistic observation group—at a ratio of 1:1:1. By designing a three-arm study and choosing online psychoeducation and naturalistic observation as comparators, we aim to minimize the influence of digital placebo effect and the natural remission of subclinical depression. The intervention period of the study is 8 weeks. Following the completion of the intervention period, the participants will be continuously followed up for 1 year. All assessments will be conducted remotely using a social media app (WeChat) to send out notifications to participants. At each follow-up time window, a notification will be sent out via the WeChat public account to remind the participant to fill out a set of self-report scales. The participants will be asked to report general information, symptom severity, social functioning, childhood traumatic experiences, parenting experiences, attachment, and coping style at the baseline and to report their symptom severity and social functioning at each follow-up time point. After the baseline assessment, the participants will be assessed at 2, 4, and 6 weeks after they started to receive the intervention and a post-intervention assessment at 8 weeks. After that, participants will enter the follow-up phase and will be assessed at 12-week, 6-month, 9-month, and 12-month follow-up time points. See Figure 1 for a flowchart demonstrating the study procedure in detail. The study has been registered as a clinical trial on the Chinese Clinical Registry website (Registration number: ChiCTR2000034826).

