### Outcome Measures and Data Collection Procedure

The follow-up procedure has been summarized in Table 2, including the outcome measures and the assessment time points of the study. Other information includes demographics information, medical history, and current treatment plan, which will be collected by questionnaires via WeChat public account. The adverse events will be assessed by participants' self-report and documented by the research team.

**Table 2 T2:** Measures and visit time point of outcome assessment.

**Visit time point**	**Visit 1 (−7 to 0 days)**	**Visit 2 (day 0)**	**Visit 3 (14 ± 2 days)**	**Visit 4 (28 ± 2 days)**	**Visit 5 (42 ± 2 days)**	**Visit 6 (56 ± 7 days)**	**Visit 7 (84 ± 7 days)**	**Visit 8 (6 months ± 14 days)**	**Visit 9 (9 months ± 14 days)**	**Visit 10 (12 months ± 14 days)**
Informed consent	×									
Patient general demographics	×									
Medical history	×									
Physical and nervous system examination	×									×
DSM-IV diagnosis	×									×
Inclusion and exclusion criteria	×	×								
General information collection form		×	×	×	×	×	×	×	×	×
PHQ-9	×	×	×	×	×	×	×	×	×	×
GAD-7		×	×	×	×	×	×	×	×	×
ASRM		×	×	×	×	×	×	×	×	×
LES		×	×	×	×	×	×	×	×	×
CTQ		×								
IPPA		×								
EMBU		×								
CSQ		×								
Treatment status		×	×	×	×	×	×	×	×	×
Adverse events	×	×	×	×	×	×	×	×	×	×
Adherence to intervention			×	×	×	×				
Satisfaction and acceptability for the intervention			×	×	×	×				

*DSM-IV, Diagnostic and Statistical Manual of Mental Disorders (Fourth Edition); PHQ-9, Patient Health Questionnaire; GAD-7, Generalized Anxiety Disorder-7; ASRM, Altman Self-Rating Mania Scale; LES, Life Event Scale; CTQ, Childhood Trauma Questionnaire; IPPA, Inventory of Parent and Peer Attachment; CSQ, Coping Style Questionnaire*.

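### Breslow is named for the time-to-response Cox model and the exact method only as sensitivity analysis, although response can be seen at only four visits; with visit-coded times this pulls the hazard ratio towards 1 and costs power

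*Protocol article*

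**What the plan says.** All of this is in the protocol article.

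- **Main comparison (Statistical Consideration).** "The Cox proportional hazard regression model using the Breslow method will be used to compare estimated time to response between groups", with adjustment for covariates.
- **Ties (same section).** "also we would use the exact method as sensitive analysis in case of tied survival data".
- **Endpoint (same section).** Kaplan–Meier is used to "calculate the estimated time from baseline to response during 8 weeks' follow-up".
- **Schedule (Study Design).** "the participants will be assessed at 2, 4, and 6 weeks after they started to receive the intervention and a post-intervention assessment at 8 weeks". Table 2 gives windows of ±2 days for the first three of these visits (for example "Visit 3 (14 ± 2 days") and ±7 days for the fourth.
- **Sample Size.** 80% power at two-sided alpha 0.025 for a 14% difference at 8 weeks in a survival analysis, 20% attrition, 145 per group. No control response rate or hazard ratio is given.
- **After week 8 (Statistical Consideration).** Because visits are then far apart, a maximum likelihood Cox method from a cited source is added "to control left interval truncated data".

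**The concern.** The plan treats ties as something that may or may not happen, but its own schedule produces them. Over 8 weeks there are four occasions on which response can be seen. If response time is the visit at which it is first seen, all responders share four values. Breslow is the common tie method that does worst in that setting. The article assigns it to the comparison on which the sample size is based and gives the better method a supporting role. At stake are an understated treatment effect and avoidable loss of power in a superiority trial.

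**Working it through.** **Inputs.** From Sample Size: 145 per arm, 20% attrition, two-sided alpha 0.025 (critical value 2.241), 14-point difference. From Study Design: four visits. Assumptions: the control response rate at week 8 (not stated, so varied), constant proportional hazards, no covariates, one pairwise comparison.

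**The plan's own figure.** 145 × 0.8 = 116 evaluable per arm. With the pooled two-proportion formula at 7% vs 21%:

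n = [2.241√(2 × 0.14 × 0.86) + 0.842√(0.07 × 0.93 + 0.21 × 0.79)]² / 0.14² = (1.100 + 0.404)² / 0.0196 ≈ 115.5, so 116, and 116/0.8 = 145.

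The same formula gives 145 at 79% vs 93%. Schoenfeld's formula gives 145 at 9% and 144 at 74%. Between these rates more are needed, up to about 303 per arm at 43%. The stated inputs alone therefore do not fix the control rate, and both low and high rates fit the stated size.

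**What Breslow estimates with four tied times.** Let P be the week-8 response probability in an arm. Under a constant hazard, the chance of responding at each visit among those still at risk is p = 1 − (1 − P)^(1/4). The Breslow score equation sets the sum over visits of d₁ − d·n₁r/(n₀ + n₁r) to zero, where d₁ is the MoodBox responders at a visit, d all responders, n₁ and n₀ the numbers at risk, and r the hazard ratio. With expected counts (d₁ = n₁p₁, d₀ = n₀p₀) the solution is r = p₁/p₀, whatever the attrition. The true hazard ratio is ln(1 − P₁)/ln(1 − P₀).

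Example, 43% vs 57%: p₀ = 1 − 0.57^0.25 = 0.131 and p₁ = 1 − 0.43^0.25 = 0.190. Breslow gives 0.190/0.131 = 1.45; the true value is 0.844/0.562 = 1.50.

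**Power.** 2,000 simulated trials per row, visit-coded times, two-sided Wald test at 0.025. The exact method was within 0.5 points of Efron in every row.

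| Control / MoodBox at week 8 | p₀, p₁ | True HR | Breslow p₁/p₀ | Power, Breslow | Power, Efron | Loss (points) |
|---|---|---|---|---|---|---|
| 7 / 21% | 0.018, 0.057 | 3.25 | 3.18 | 81.6% | 82.6% | 1.0 |
| 10 / 24% | 0.026, 0.066 | 2.61 | 2.55 | 73.5% | 75.4% | 1.9 |
| 20 / 34% | 0.054, 0.099 | 1.86 | 1.82 | 58.0% | 62.0% | 4.0 |
| 30 / 44% | 0.085, 0.135 | 1.63 | 1.58 | 47.4% | 52.6% | 5.2 |
| 43 / 57% | 0.131, 0.190 | 1.50 | 1.45 | 41.7% | 50.1% | 8.4 |
| 60 / 74% | 0.205, 0.286 | 1.47 | 1.40 | 48.2% | 59.8% | 11.6 |
| 74 / 88% | 0.286, 0.411 | 1.57 | 1.44 | 67.5% | 84.1% | 16.6 |
| 75 / 89% | 0.293, 0.424 | 1.59 | 1.45 | 71.0% | 86.4% | 15.4 |

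Repeat runs of this design widen the loss to 8-10 points at 43%, 12-16 at 60% and 13-17 at 74-75%. Simulated mean hazard ratios agree with the closed form: at 74/88%, Breslow 1.44, Efron 1.56, exact 1.58. At 7%, with about 35 events, the attenuation is lost in small-sample error (Breslow 3.31, Efron 3.37, true 3.25).

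**Why the test is conservative.** Breslow treats the number of tied responders at a visit as Poisson, with variance np. It is binomial, with variance np(1 − p). The standard error is therefore too large for the Breslow estimate by about 1/√(1 − p). With equal arms at 75%, p = 0.293 and the factor is 1.19; the simulated ratio was 1.20. Simulated rejection under the null, against a nominal 2.5%, was 1.7% (Breslow) vs 2.75% (Efron) at 43%, and 0.45% vs 2.2% at 75%.

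**If actual days are analysed.** The windows allow 3 × 5 + 15 = 30 possible days, so ties are fewer. Power, Breslow vs Efron: 49.4% vs 50.9% at 43/57%, 55.6% vs 58.1% at 60/74%, 77.6% vs 80.8% at 74/88%.

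**The case against.** **Nominal visit times are an assumption.** The article does not say how time is coded. Scales are completed on phones and go directly into the data capture system, so actual dates should exist, and with them the loss is about 3 points or less. This stands, and the point is conditional for that reason. The article does not exclude visit coding either.

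**The size rests on a missing input.** This also stands. At control rates of 10% or below, which are compatible with 145 per group, the effect is negligible.

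**The plan already includes the exact method.** True, and a discrepancy would become visible. The main result would still rest on Breslow.

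**No false claim of efficacy follows.** Correct: the error is conservative. It still biases the estimate and wastes power.

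Some stronger readings are tempting but not supported:

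- *Breslow will report a wider standard error.* The printed value is almost the same as Efron's (0.139 for both at 74/88%). It is too large only relative to the variability of the attenuated Breslow estimate (0.113). Changing method moves the estimate, not the printed error.
- *Breslow explains low power in this trial.* At middle control rates power is near 50% even with Efron or exact. That shortfall comes from the sample-size assumptions.
- *The post-week-8 model uses a wrong likelihood.* That depends on a cited source that is not at hand.
- *Cox is declared the primary analysis.* Primary Outcome defines efficacy by item scores at the post-treatment assessment. It is Sample Size that links the primary outcome to a survival analysis, and Statistical Consideration does not call the Cox model primary.

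**Conclusion.** The point holds in conditional form. If response time is coded by visit, Breslow is a poor choice for the main comparison of time to response to week 8. The log hazard ratio is understated by about 8-9% at a 43% control rate (1.45 for 1.50) and about 20% at 74% (1.44 for 1.57), and the test is conservative. The power loss against Efron or exact is about 1-2 points at control rates of 7-10%, 4-5 at 20-30%, 8-10 at 43%, 12-16 at 60% and 13-17 at 74-75%. At 74%, where 145 per group agrees with 80% power by Schoenfeld's formula, Breslow alone takes power from 84% to about 68%. With actual assessment days the loss is at most about 3 points.

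These figures assume 145 per arm, a 14-point difference, 20% attrition, proportional hazards and no covariates.

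The truncation term is a wording matter only. Time runs from baseline and no delayed entry is described. The reason given, long gaps between visits, is the usual description of interval censoring.

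**What to change.** 1. In Statistical Consideration, swap the two tie methods. Make the exact method (or Efron, or a discrete-time complementary log-log model on the visits) the main analysis of time to response to week 8. Keep Breslow, if at all, as sensitivity analysis.
2. State whether response time is the scheduled visit or the actual assessment day.
3. Replace the truncation term for the post-week-8 data with interval censoring, or explain what is truncated.

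The sponsor already plans to run both tie methods, so the first change is a matter of roles: a sentence in the plan and one option in the SAS program. The other two are wording. No participants, visits or data are added. All three should be settled before outcome data are analysed.

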## Abstract

**Background:** Subclinical depression is a prevalent mental health problem and increases the incidence of the onset of major mood disorders, such as major depressive disorder (MDD). Psychological interventions have been proved to be effective for reducing depressive symptoms for people with subclinical depression and can prevent the onset of MDD. However, people have limited access to face-to-face psychotherapy. Internet-based psychological intervention is an alternative treatment option. The aim of the study is to evaluate the efficacy of MoodBox, an online psychological intervention program, for subclinical depression.

**Methods:** This study is a multicenter, randomized, controlled, non-blinded superiority study with three parallel groups. A total of 435 first-year university students with subclinical depression will be recruited. Eligible participants will be randomly assigned to the MoodBox group, the online psychoeducation group, and the naturalistic observation group at a ratio of 1:1:1. The intervention period is 8 weeks, and participants will be continuously followed up for 1 year. The primary outcome of the study is the efficacy of the intervention, defined as measured by the Patient Health Questionnaire (PHQ-9).

**Discussion:** This is the first study to innovatively develop and test an intervention to improve psychological well-being and decrease the incidence of MDD in a subclinical depression population in China. Once proven effective and acceptable, MoodBox could be potentially integrated into the routine clinical service to facilitate the management for people with subclinical depression.

**Clinical Trial Registration:** The trial is registered with the Chinese Clinical Trial Registry on 21 July 2020 (No. ChiCTR2000034826).

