### Participation Eligibility

The eligibility of participants will be assessed in accordance with the following inclusion and exclusion criteria by psychiatrists through clinical interview and relative scales. The inclusion criteria are (1) age 18 years or older, no restriction for gender; (2) the score of two to four items on the Patient Health Questionnaire (PHQ-9) scale ≥ 2 (must include the first or second item, which are the indicator for core symptoms of depression) and a total score ≤ 9; (3) not meeting diagnostic criteria for any mental disorders according to the *Diagnostic and Statistical Manual of Mental Disorders* (Fourth Edition) (DSM-IV); and (4) being able to give consent. The exclusion criteria are (1) having severe and unstable physical illness; (2) having organic brain damage; or (3) being alcohol or drug dependent. A psychiatrist will be using Mini-International Neuropsychiatric Interview (MINI) to rule out any mental disorders. The exclusion criteria will be assessed through clinical interview by completing a screening checklist of the study.

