### Recruitment and Randomization

The study is a multicenter, three-arm, parallel RCT. The study will be conducted at three universities in Beijing, China. First-year students who are waiting for the regular physical examination will be invited by research staff to complete a brief screening questionnaire to assess their eligibility. Students who meet the eligibility criteria will be provided with the participant information sheet and the consent form of the study. If the participants were interested in participating in the study, research staff would give a more comprehensive face-to-face explanation of the study in a private consultation room. Written consent will be required before the participant formally enrolls in the study. Eligible participants will be randomly assigned to three groups—the MoodBox group, the online psychoeducation group, or the observation group—with a ratio of 1:1:1. Randomization will take place after the completion of baseline assessment using a randomization code, which will be developed in SAS 9.4 (SAS Institute Inc., Cary, NC, USA) by a statistician who is not involved in the study.

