#### Primary Outcome

The primary outcome is the efficacy of the intervention measured by the PHQ-9 (22). PHQ-9 is a nine-item reliable and valid self-report depression severity screening and diagnostic tool based on the DSM-IV criteria (23, 24). Response options are “not at all,” “several days,” “more than half the days,” and “nearly every day,” scored as 0, 1, 2, and 3, respectively (total score range from 0 to 27). In the current study, efficacy is defined as the participants score ≥ 2 on less than two items on the PHQ-9 scale at post-treatment assessment. PHQ-9 has demonstrated high reliability and validity in the Chinese population, with Cronbach's alpha for the internal consistency reliability being 0.86, the correlation coefficient for the 2-week test–retest of the total score being 0.86, and positive correlation with the Self-Rating Depression Scale (SDS; *r* = 0.29, *p* < 0.001) and the 36-item Short Form Health Survey (SF-36; correlation coefficients ranged from −0.11 to −0.47, *p* < 0.001) (25).

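### The Cox model names near-constant covariates (age, years of education) but not the baseline PHQ-9 item count, which sets how far each participant must improve to respond

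*Protocol article*

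**What the plan says.** The protocol article, under Statistical Consideration, compares time to response between groups by Cox regression with Breslow handling of ties, "with control for covariates such as age, gender, years of education, and disease-related conditions". The list is illustrative, and the last item is not defined. Neither baseline PHQ-9 nor university is named.

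The other parts that bear on this are:

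- **Population.** The Abstract states: "A total of 435 first-year university students with subclinical depression will be recruited". Recruitment and Randomization confirms it: "First-year students who are waiting for the regular physical examination will be invited". The age criterion is "age 18 years or older, no restriction for gender", with no upper limit.
- **Entry.** Participation Eligibility requires two to four PHQ-9 items scored 2 or more: "must include the first or second item, which are the indicator for core symptoms of depression) and a total score ≤ 9".
- **Response.** Under Primary Outcome, the participant must score 2 or more "on less than two items on the PHQ-9 scale at post-treatment assessment".
- **Availability.** Table 2 schedules the PHQ-9 at Visit 1 (screening) and Visit 2 (day 0).
- **Allocation.** "Randomization will take place after the completion of baseline assessment using a randomization code". No stratification by PHQ-9 or by university is stated.

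**The concern.** A covariate earns its place in the primary model by predicting the outcome. Two of the three specific covariates named suit a general adult sample. In a single academic year they should be close to constant, so they can explain almost nothing. This is an inference, because the article gives no spread for either.

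The baseline quantity tied most directly to the endpoint goes unnamed. Entry and response are both defined by the number of PHQ-9 items scored 2 or more, so the starting count fixes the distance to response. If the count stays out of the model, any chance difference between arms in starting severity carries into the estimated hazard ratio, and some power is given up although the data are already being collected.

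**Working it through.** **1. Distance to response.** Response means at most one item scored 2 or more. The net fall needed is the starting count minus one: 2 − 1 = 1, 3 − 1 = 2, 4 − 1 = 3.

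**2. How prognostic that could be (illustration).** Assume that each such item remits independently with probability 0.4 and that no new one appears.

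- Two items, at least one remits: 1 − 0.6² = 0.64.
- Three items, at least two remit: 3(0.4²)(0.6) + 0.4³ = 0.288 + 0.064 = 0.352.
- Four items, at least three remit: 4(0.4³)(0.6) + 0.4⁴ = 0.1536 + 0.0256 = 0.179.

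On the complementary log-log scale, which corresponds to a log hazard ratio, log(−log(1 − p)) is 0.02, −0.83 and −1.62. That is roughly −0.8 to −0.9 per item. Correlated items or newly emerging symptoms would weaken it.

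**3. The plan's own figure.** Sample Size gives 145 per group, with 80% power, two-sided alpha 0.025, a 14-point difference and 20% attrition. This implies 145 × 0.8 = 116 evaluable. The control rate is not stated. The pooled two-proportion formula

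n = [z₁₋α/₂ √(2p̄(1−p̄)) + z₁₋β √(p₁(1−p₁) + p₂(1−p₂))]² / d²

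reaches 116 at, for example, 7% versus 21%:

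[2.241 × √0.2408 + 0.842 × √0.2310]² / 0.0196 = 115.5, so 116, and 116 / 0.8 = 145.

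The match depends on choosing that rate, and no covariate enters the calculation. Adjustment therefore neither supports nor undermines the 145.

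**4. Effect of adjusting, in the planned model type.** The simulations used a Cox model with Breslow ties, four visits to week 8, 116 per arm and two-sided alpha 0.025 (|z| > 2.241). The comparator is an unadjusted model. Response rates, baseline mix and prognostic strength are assumptions.

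*Adjusting for item count* (50/30/20% starting with 2/3/4 items; 1,200 trials per cell):

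| Log-HR per item | 40% vs 54%: power without → with | 16% vs 30%: power without → with |
|---|---|---|
| −0.3 | 39 → 41% | 56 → 57% |
| −0.5 | 37 → 39% | 58 → 60% |
| −0.8 | 39 → 44% | 58 → 61% |
| −1.0 | 39 → 49% | 59 → 63% |

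The largest gain is about 9 points; the two powers in that cell are rounded separately.

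*Adjusting for a standardised baseline score* (2,500 trials per cell):

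| HR per SD | 16% vs 30% | 50% vs 64% |
|---|---|---|
| 1.00 | 59.6 → 59.6% | 39.0 → 38.8% |
| 0.82 | 59.2 → 59.7% | 39.4 → 40.6% |
| 0.70 | 57.3 → 58.9% | 39.1 → 42.3% |
| 0.61 | 57.9 → 61.8% | 40.2 → 45.4% |

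Here the gain is about 0 to 5 points. Adding university changed power by less than 1 point.

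**5. Where the gain comes from.** At 50% versus 64% with HR 0.61 per SD, the mean log hazard ratio moved from 0.354 to 0.378, while its standard error went from 0.176 to 0.177. The ratio rises from 0.354 / 0.176 = 2.01 to 0.378 / 0.177 = 2.14. The estimate moves; the standard error does not fall.

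**6. A limit on the gain.** Four items scored 2 or more use at least 4 × 2 = 8 points, so under the cap of 9 such a participant can total only 8 or 9. Of the 13,010 response patterns that satisfy the entry rule, 910 (910 / 13,010 = 7%) have four such items. This counts patterns and does not estimate prevalence, but it suggests that a 20% share with four items may be generous. Under a 65/30/5% mix with 116 per arm, a logistic version of the comparison gave a gain of about 2 to 5 points.

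**The case against.** The best defence is that the list is open and that baseline severity is a natural reading of disease-related conditions in a subclinical depression trial. **This stands in part.** A reader might infer that the plan excludes baseline PHQ-9, but the text does not establish that; it only fails to name it. If the phrase already means the PHQ-9 item count, the gain computed above is already in the plan and only the wording needs attention.

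Second, this is a condensed article, and an analysis plan that is not shown may close the list. **This also stands.** An open list is not a fault by itself here. What remains is that the article chose which covariates to name, and those it chose suit this population poorly.

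Third, a reader might take adjustment to be free precision. The simulations do not support that: the standard error is unchanged, and the hazard ratio becomes a conditional one, which is a different estimand.

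Fourth, a larger gain, 4 to 10 points, can be produced from a logistic model with 145 per arm. That model ignores the predicted 20% attrition and is not the planned analysis, so it should not be relied on.

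Fifth, chance imbalance under randomisation is not bias and is already allowed for in the type I error. That is correct. The argument for adjustment is that it takes the realised imbalance out of the estimate.

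Last, "The study will be conducted at three universities in Beijing, China", and a reader might conclude that university must be in the model. No stratification by university is stated, and adding it changed power by less than 1 point, so this is optional. Keeping weak covariates such as age does negligible harm.

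**Conclusion.** The point holds as a modest improvement to the primary model; it is not an error that threatens validity. The named covariates include two that should be nearly constant in first-year students. The baseline PHQ-9 item count, which entry and response jointly make the distance to the endpoint, is not named.

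Adjusting for it raises power by about 0 to 9 percentage points with 116 per arm and alpha 0.025. The low end applies if baseline is weakly prognostic. The high end needs a log hazard ratio near −1.0 per item and a fairly large group starting with four items. The rates, mixes and strengths are all assumptions, and the comparison is with an unadjusted model. The near-constancy of age and education is inferred from the population.

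**What to change.** In Statistical Consideration, name the Visit 2 number of PHQ-9 items scored 2 or more as a prespecified covariate in the primary Cox model, in place of years of education. Say whether disease-related conditions was meant to include baseline PHQ-9. State that the reported treatment effect is a hazard ratio conditional on the covariates in the model. University may be added but need not be.

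The cost is a change of wording, made before outcome data are examined. No new data, visits or participants are needed, since the PHQ-9 is already scheduled at Visit 2.
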